**Table 2 Tab2:**
[figure not shown]
The schedule of enrollment, interventions, and assessments

The safety assessment comprises a routine blood test, routine urine test, routine feces test, kidney function test, liver function test, and electrocardiogram

*SAS* Self-Rating Anxiety Scale, *SDS* Self-Rating Depression Scale, *PSQI* Pittsburgh Sleep Quality Index, *POMS* Profile of Mood States Scale, *PANAS* Positive and Negative Affect Schedule Scale, *EA* electroacupuncture treatment, *Mass* Massachusetts General Hospital Acupuncture Sensation Scales

**Fig. 3 Fig3:**
[figure not shown]
The SD study participants’ timeline of activities and assessments during hospitalization

### Sample size {14}

This is an RCT study with three groups: an AE group, a NAE group, and a blank control group. The POMS will be the primary outcome measure observed. According to the findings of the clinical pre-trial study, the means of the POMS scores for each group are 8.26, 18.25, and 15.24, with standard deviations of 3.18, 5.96, and 5.42, respectively. The sample size was calculated by the PASS software (version 15.0.5, NCSS, LLC) [39], and at least 33 subjects will be needed in our study if the power is 0.9 and *α* is set to 0.05. To compensate for a 20% loss to follow-up, the sample size will be increased to 42 participants, of which at least 14 participants will be required in each group.

### Recruitment {15}

Several strategies will be applied in participant recruitment. Forty-two healthy male volunteers will be recruited by advertisement on notice boards at local Chinese universities. Advertisements will be placed across WeChat and websites. The posters and advertisements will contain brief introductions about the population to be enrolled, the free acupuncture treatments offered to volunteers, and the contact information of the researchers. All subjects will be required to sign a written informed consent before participating and will be monetarily compensated.

### Assignment of interventions: allocation

#### Sequence generation {16a}

Randomization will be done using the Excel random number method. The participating volunteers will be strictly screened according to the inclusion and exclusion criteria. Once inclusion is confirmed, participants will be numbered in the order by which they will be included. Random numbers will be generated by the rand function using Excel numbering after which they will be fixed and reordered.

#### Concealment mechanism {16b}

Randomization will be performed by a person who will not be engaged in the study in order to blind the identity of the participants.

#### Implementation {16c}

The randomization sequence will be generated using a random number table by an independent statistician. A sealed envelope will be used to hide the group assignments. Then, the envelopes will be numbered in sequential order and stored by a research assistant who will not be involved in the enrollment process. When an eligible volunteer is enrolled in the study, an envelope will be opened by research assistants that will be responsible for enrolling the volunteers.

### Assignment of interventions: blinding

#### Who will be blinded {17a}

Blinding methods will be applied to data statisticians and outcome evaluators throughout the trial. They will not be able to obtain information regarding the grouping and treatment of participants. Acupuncturists will not be masked due to the nature of acupuncture. However, acupuncturists will not participate in the data collection, statistics, and final outcome evaluation. For the intervention, different volunteers will be assigned to different treatment rooms with independent beds so as to avoid contact among subjects. Personnel in charge of random grouping, acupuncture treatment, data processing, and outcome evaluation will be completely separated so as to ensure the authenticity of the outcome of the trial to the greatest possible extent.

#### Procedure for unblinding if needed {17b}

At the end of the trial, we will first perform a first blinded unblinding to clarify the differences between the 3 groups, but will not know the content of the interventions in the 3 groups, on the basis of which statistical analysis will be performed. A second unblinding will then be performed, which will reveal which group is the AE group, which group is the NAE control group, and which group is the blank control group, to further analyze the results of the clinical trial. However, researchers will be permitted to be unblinded before the end of this trial in some specific situations, such as participants experiencing serious adverse events or disease progression, and where prompt treatment and appropriate management are needed. The procedure for unblinding will be as follows: (1) prior to unblinding, the researcher will need to inform the trial steering committee; (2) the researcher should unblind the intervention information of the patient based on the emergency envelope; and (3) the researcher will need to fill out the report form of unblinding and note it on the case report form (CRF).

### Data collection and management

#### Plans for assessment and collection of outcomes {18a}

Prior to the start of the trial, all data assessors will be uniformly trained in order to improve the quality of the data assessment. The primary outcome measure will be obtained using POMS while the secondary outcome measures will be obtained using PANAS and FaceReader. These three instruments have been widely used in trials related to the detection of mood changes [36–38]. During the 30-h TSD period, participants will be assessed every 3 h for a total of 11 assessments. During the 24-h after waking follow-up period, participants will also be assessed once.

#### Plans to promote participant retention and complete follow-up {18b}

During the recruitment period, participants will receive extensive information about the clinical trial requirements. The importance of completion of the follow-up will be stressed. Participants will be allowed to discontinue the study at any time and will not be obliged to give a reason for their discontinuation. Throughout the study, participants will be reminded to fill out the questionnaires during study visits, while during the follow-up period, investigators will check the responses and if necessary contact the participants for completion of their follow-up.

#### Data management {19}

A special data collector will record the participants’ personal data in the CRF. At least 5 completed CRFs from each clinical trial center shall be sent to the data manager in a timely fashion by the supervisor so as to establish a corresponding database. Epidata 3.1 (EpiData Association, Denmark), which is a statistical package, will be used for data entry. All data will be double entered using the data entry program run on a software platform. The data administrator shall ensure that the data in the CRF forms are completely and truly entered into the computer.

#### Confidentiality {27}

Only researchers will have access to the personal data in the trial. These data will not be published, and they will be discarded after the publication of the results.

#### Plans for collection, laboratory evaluation, and storage of biological specimens for genetic or molecular analysis in this trial/future use {33}

This is not applicable. Researchers confirm that there will be no laboratory and storage of biological specimens for genetic or molecular analysis in this study.

## Statistical methods

### Statistical methods for primary and secondary outcomes {20a}

Descriptive statistics will be used to describe the study population. Comparisons of the study groups by age, gender, and outcome characteristics will be done using analysis of variance (ANOVA) or chi-square tests. Depending on whether the data are normally distributed, the continuous variables will be described as the mean (standard deviation) or the median. One-way analysis of variance (ANOVA) will be used for comparisons among the three groups. Continuous variables, including the POMS scores, PANAS scores, and FaceReader, will be compared among the three groups at all time points using ANOVA. The Student-Newman-Keuls method will be used for pairwise comparisons. Adverse events will be summarized for each group and compared using Fisher’s exact tests. Statistical analyses will be performed using SAS 9.1.3. Statistical significance will be set at *p* ≤ 0.05.

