**Methods:**

This randomized controlled trial (RCT) will be performed at the First Affiliated Hospital of Changchun University of Chinese Medicine in China. The Standards for Reporting Interventions in Clinical Trials of Acupuncture 2010 will be strictly adhered to. Forty-two healthy male volunteers will be distributed into acupoints electroacupuncture (AE) group, non-acupoints electroacupuncture (NAE) control group, or blank control group. This trial will comprise 1-week baseline (baseline sleep), 1-week preventative treatment, 30-h total sleep deprivation (TSD), and 24-h after waking follow-up period. Participants in the AE group and the NAE control group during the preventative treatment period will be administered with EA treatment once daily for 1 week. Participants in the blank control group will not be administered with any treatment. The primary outcome will be the Profile of Mood States (POMS) Scale. Secondary outcome measures will include changes in the Noldus FaceReader (a tool for automatic analysis of facial expressions) and Positive and Negative Affect Schedule (PANAS) Scale. Total sleep deprivation will be 30 h. During the 30-h TSD period, participants will be subjected to 11 sessions of assessment. Adverse events will be recorded.

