#### Secondary outcomes

##### Positive and Negative Affect Schedule Scale

The PANAS [37] will be used to assess the positive and negative effects. Participants will be shown 20 adjectives with 10 describing positive moods and 10 describing negative moods. They will respond using a 5-point Likert scale (1 very slightly, 5 extremely).

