##### Noldus FaceReader

The Noldus FaceReader software (FR; version 7.0, Noldus Information Technology) [38] is a facial analysis program that detects emotional facial expressions in film and photographs. The FaceReader can detect six basic emotions, happiness, sadness, anger, fear, surprise, and disgust, as well as neutral states. The FaceReader can also analyze the valence of facial expressions as well as the general state of arousal. The video stimuli are analyzed frame-by-frame to detect the intensity by which each of the six basic emotions is expressed on a scale of 0 to 1, where 0 indicates the absence of emotion while 1 indicates maximum intensity. In this study, the focus will be on the participants’ emotions after sleep deprivation. Prior to analysis, all videos will be calibrated to each participant’s own neutral expression to achieve the most accurate results. The videos will then be analyzed using the batch analysis mode, which sequentially analyzes each video without the need for supervision. Videos of participants’ facial expressions will be recorded using Logitech HDC 920 PRO Webcam, which will be placed above the computer screen. The videos will be processed using the Noldus FaceReader software and Observer XT (version 12.5, Noldus Information Technology). The software’s artificial intelligence is trained to register the activation of 20 action units (AUs) and to indicate scores for happiness, surprise, anger, sadness, disgust, and scared faces as proposed by the basic emotion framework.

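### PANAS and FaceReader outcomes are tested at the same p ≤ 0.05 as POMS, at all time points, with no order, adjustment or exploratory label

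*Protocol article*

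**What the plan says.** Section {20a} of the Protocol article sets the analysis for all three instruments in one sentence: "Continuous variables, including the POMS scores, PANAS scores, and FaceReader, will be compared among the three groups at all time points using ANOVA". One threshold follows for everything: "Statistical significance will be set at *p* ≤ 0.05". The only multiple-comparison device is for pairs of arms: "The Student-Newman-Keuls method will be used for pairwise comparisons".

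The outcomes are ranked elsewhere. The abstract states "The primary outcome will be the Profile of Mood States (POMS) Scale", and section {18a} states "The primary outcome measure will be obtained using POMS while the secondary outcome measures will be obtained using PANAS and FaceReader". The sample size section {14} rests on POMS alone.

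On the number of secondary measures, the PANAS section says "Participants will be shown 20 adjectives with 10 describing positive moods and 10 describing negative moods", which gives a positive and a negative score. The FaceReader section says "The FaceReader can detect six basic emotions, happiness, sadness, anger, fear, surprise, and disgust, as well as neutral states" and adds "The FaceReader can also analyze the valence of facial expressions as well as the general state of arousal". It does not say which of these outputs will be tested.

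Section {18a} gives 11 assessments during the 30-hour deprivation and one at follow-up. The section on additional analyses {20b} says only that no interim analyses are planned.

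**The concern.** The article does not leave secondary testing open. It fixes a rule under which every PANAS and FaceReader measure may be declared significant at 0.05 at every time point. The Student-Newman-Keuls step works among the three arms within one outcome at one time and does nothing across outcomes or times. Nothing in the article orders the secondary outcomes, adjusts across them, makes them depend on POMS or marks them as exploratory.

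Three features of this trial make that matter more than usual:

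- FaceReader is the only efficacy outcome that is not self-rated, and blank-control participants know that they receive no treatment. A chance FaceReader difference would therefore be read as objective support.
- The objective is prevention of negative moods, yet outputs such as happiness and surprise fall under the same significance rule as sadness or anger.
- The objectives section {7} also plans to compare effects at different time points, which invites reporting of isolated significant times.

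Defining one POMS score and one POMS time would leave the secondary family unchanged.

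**Working it through.** **The plan's own figures.** The article gives no multiplicity figure to reproduce. Its sample size supplies the number per arm used below. Inflating 33 for 20% loss gives 33 / 0.8 = 41.25, rounded up to 42, or 14 per arm, as stated. The 33 can be matched by a normal-approximation comparison of AE with blank. The difference is 15.24 − 8.26 = 6.98, and the pooled SD is √((3.18² + 5.96² + 5.42²)/3) = 5.00. Then n = 2 × (1.960 + 1.282)² × 5.00² / 6.98² ≈ 10.8, so 11 per arm and 33 in all. The article does not name the procedure used, and the present point does not depend on it.

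**Inputs**

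| Input | Value | Source |
|---|---|---|
| Threshold per test | 0.05 | {20a} |
| PANAS scores | 2 | PANAS section |
| FaceReader emotions | 6 (neutral, valence and arousal would make 9) | FaceReader section |
| Assessments | 11 + 1 = 12 | {18a} |
| Participants per arm | 14 | {14} |
| Correlation between outcomes and between times | not given; 0 to 0.8 assumed | assumption |

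**One fixed time, 8 tests (2 + 6).** If the tests are independent, the chance of at least one false positive is 1 − (1 − 0.05)^8 = 1 − 0.95^8 = 33.7%. With equal correlation between outcomes, null normal data, 14 per arm and a one-way ANOVA F test at 0.05, simulation gives:

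| Correlation | 0 | 0.2 | 0.3 | 0.5 | 0.7 | 0.8 |
|---|---|---|---|---|---|---|
| At least one false positive, 8 tests | 34% | 32% | 31% | 26% | 20% | 16% |

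For the six emotions alone, independence gives 1 − 0.95^6 = 26.5%, and simulation gives about 25%, 21% and 17% at correlations 0.3, 0.5 and 0.7.

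**All 12 assessments, as {20a} reads.** The count is 8 × 12 = 96 omnibus tests. Independence gives 1 − 0.95^96 = 99.3%. The simulation uses the same correlation between outcomes and between times, with their product applying to different outcomes at different times. It gives about 99%, 89% and 51% at correlations 0.2, 0.5 and 0.8. The expected number of false positives is 96 × 0.05 = 4.8, whatever the correlation. With the 11 deprivation assessments only, the count is 8 × 11 = 88, and 88 × 0.05 = 4.4 are expected.

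**How many tests for even odds.** ln(0.5) / ln(0.95) = 13.5, so about 14 independent tests are needed for the chance to pass 50%. Eight tests at one time stay below that.

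**The case against.** The strongest reply is that this is ordinary practice. Secondary outcomes are often tested without adjustment, the secondary label already signals support rather than confirmation, and a hierarchy may sit in an analysis plan that is not shown. The 0.05 in {20a} is also a per-test threshold and not a promised family-wise rate. This lowers the weight of the point but does not remove it. The article states a rule, all instruments at all times at one threshold, and the point is against that rule.

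Several stronger readings are tempting, and the documents do not support them:

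- A reader might infer that PANAS and FaceReader have the same standing as POMS. They do not: the abstract, the outcomes section and {18a} rank them, and the trial is sized on POMS alone. Only the test and the threshold are shared.
- A reader might infer that a false-positive emotion is likely even at one fixed time. At about 17–26% for the six emotions it is well above 5% but below even odds.
- A reader might count 11 secondary endpoints. Neutral, valence and arousal are described as things the software can report and are not listed as tested outcomes.
- A reader might think that the pairwise tests add further inflation. With three arms, Student-Newman-Keuls holds the error within each outcome and time.
- A reader might suppose that the secondaries are meant to rescue a negative POMS result. No section says so.

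Two further limits stand. The schedule table is not shown, so use of every instrument at all 12 assessments is a reading of {18a} and {20a} together. Most of the step from 16–34% to near certainty comes from repeated testing over time, which affects POMS equally and should not be counted twice.

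**Conclusion.** The point holds as a should-change matter. Section {20a} applies the primary outcome's test and threshold to at least eight secondary measures at all time points without ordering, adjusting or labelling them. With one time fixed, the chance of at least one false positive is about 16–34%, roughly three to seven times the nominal 5%. Tested at all 12 assessments, it is about 50% to over 99%, with about 5 false-positive ANOVAs expected if there is no effect.

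The percentages rest on assumed correlations from 0 to 0.8, normal data and 14 per arm. The expected count needs only the number of tests. The primary conclusion on POMS does not depend on this point. What is exposed is the credibility of any positive PANAS or FaceReader claim.

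**What to change.** In {20a}, limit significance claims on secondary outcomes to at most one measure of negative mood named in advance, for example PANAS negative affect. Analyse it at the same time or summary, and for the same contrast between arms, as the primary POMS analysis. Test it at 0.05 only if the POMS comparison is significant. This requires the primary POMS comparison to be a single defined test. State that all other PANAS and FaceReader outputs, and all other times, are exploratory and will be reported as estimates with 95% confidence intervals and no significance claim.

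Which measure is named and which contrast leads are for the sponsor to choose. PANAS negative affect is one reasonable option, and choosing another would not be an error.

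The change needs wording only, with no new data or participants. The downside is that an isolated PANAS or FaceReader difference can no longer be called statistically significant.

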### Outcomes {12}

#### Primary outcome

##### Profile of Mood States Scale

The POMS [36] is a well-validated, 65-item self-report measure comprising six subscales: tension/anxiety, depression/dejection, anger/hostility, energy/activity, fatigue/vigor, and confusion/bewilderment. Participants will report on their mood using a 5-point scale (“not at all” to “extremely”).

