### Participant timeline {13}

The trial will comprise 1-week baseline, 1-week preventative treatment, 30-h TSD, and 24-h after waking follow-up periods. During the 30-h TSD period, participants will be assessed every 3 h for a total of 11 sessions. They will be evaluated at 7:00 am (baseline), 10:00 am, 1:00 pm, 4:00 pm, 7:00 pm, 10:00 pm, and on the next day at 1:00 am, 4:00 am, 7:00 am, 10:00 am, and 13:00 pm. AE will also be recorded. Table 2 shows the participant timeline. The SD study participants’ timeline of activities and assessments during hospitalization is shown in Fig. 3.

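### POMS is tested by an unadjusted one-way ANOVA at every time point, with no primary score or time named, so the false-positive risk for one score is roughly 14% to 39%, not 5%

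*Protocol article*

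**What the plan says.** The primary outcome section names POMS, a "65-item self-report measure comprising six subscales", and selects neither a total score nor a subscale. The sample-size section {14} says "The POMS will be the primary outcome measure observed" and gives one mean and one SD per arm (means 8.26, 18.25, 15.24; SDs 3.18, 5.96, 5.42), without identifying the score or the time. From these it derives 33 evaluable participants at power 0.9 and alpha 0.05, raised to 42 for 20% loss.

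The participant timeline {13} says that "participants will be assessed every 3 h for a total of 11 sessions", from 7:00 am (called baseline) to 13:00 the next day. Section {18a} repeats the count of 11 and adds one assessment in the follow-up period.

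The statistical methods section {20a} sets the test ("One-way analysis of variance (ANOVA) will be used for comparisons among the three groups"), its repetition ("Continuous variables, including the POMS scores, PANAS scores, and FaceReader, will be compared among the three groups at all time points using ANOVA"), the pairwise procedure ("The Student-Newman-Keuls method will be used for pairwise comparisons") and the threshold ("Statistical significance will be set at *p* ≤ 0.05"). It gives no adjustment across times. The objectives {7} make a comparison of effects at different time points an aim and rank none of them.

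**The concern.** The sample size assumes one test of one POMS value at alpha 0.05. The analysis section specifies a series of tests of POMS, each at 0.05, and treats the primary outcome exactly as it treats PANAS and FaceReader. Because no score or time is marked as primary, the result put forward as primary could be chosen after the data are seen. At stake is the type I error of the trial's main claim: 5% describes each test, not the set.

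**Working it through.** **Inputs from the article.** Three arms, 1:1:1, 14 per arm (11 after the planned loss). 11 sessions in the deprivation period: 7:00 to 13:00 the next day is 30 h, and 30/3 + 1 = 11. One follow-up assessment. Alpha 0.05 per test. Means and SDs as in {14}, read in the order AE, NAE, blank.

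**Assumed input.** The article gives no correlation between repeated POMS ratings in the same person, so a range is used.

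**Step 1: the plan's own figure.**
- Pooled SD = √[(3.18² + 5.96² + 5.42²)/3] = 5.00.
- AE vs blank difference = 15.24 − 8.26 = 6.98.
- n per arm = 2 × (1.960 + 1.282)² × 5.00² / 6.98² = 10.8, so 11 per arm and 33 in total.
- 33/0.80 = 41.25, rounded up to 42 for equal arms.

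The stated 33 and 42 are thus reproduced by a single comparison of one POMS value at one alpha of 0.05. The article does not say which PASS procedure was used, so this shows a match and not necessarily the method.

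**Step 2: if the tests were independent.** P(at least one false positive) = 1 − 0.95^k: 40.1% for k = 10, 43.1% for k = 11, 46.0% for k = 12. Repeated ratings in the same men are correlated, so these are reference values.

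**Step 3: correlated tests.** Simulated one-way ANOVAs, 3 × 14 normal subjects, no true effect, one POMS score. Entries are the chance of at least one p ≤ 0.05.

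| Times tested | Equal corr. 0.9 | 0.7 | 0.5 | AR(1) 0.9 | 0.7 | 0.5 |
|---|---|---|---|---|---|---|
| 10 (7:00 session not counted) | 13–14% | 22–23% | 30% | 20% | 31% | 37% |
| 11 (all deprivation sessions) | 14% | 24% | 31% | 21% | 33% | 39% |
| 12 (with follow-up) | 15% | 25% | 34% | 23% | 35% | 42% |

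With 11 sessions this is 2.7 times nominal (13.5/5) at the low end and 7.8 times (39/5) at the high end.

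**Step 4: does Student-Newman-Keuls help?** Within one time point, the simulated chance of any false pairwise rejection is 4.9–5.2%. Over 11 times it is 14%, 24% and 32% at equal correlation 0.9, 0.7 and 0.5. The inflation therefore comes from the times, not from the three pairs.

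**Step 5: power if the rule is tightened.** Noncentrality of the ANOVA = n × Σ(mean − 13.92)² / 5.00² = n × 52.53/25.00.

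| Rule | 11 per arm | 14 per arm |
|---|---|---|
| One omnibus ANOVA at 0.05 | 0.99 | >0.99 |
| AE vs NAE, then AE vs blank, each at 0.05, both succeed | 0.93 | 0.98 |
| Omnibus ANOVA at 0.05/11 = 0.0045 | 0.89 (pooled SD) to 0.91 (arm-specific SDs) | 0.97 to 0.98 |

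The last row is power at a given time, if the planning difference holds at that time.

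**The case against.** The strongest reply is that this is a condensed article. A primary time, a testing order or a multiplicity rule may stand in a full protocol or analysis plan that is not shown, and the article states no success rule. It follows that no one can say a single significant session will be reported as a positive trial; a reader might infer that, but the article does not state it. What survives is narrower. The article does fix the test, its repetition at all times and an unadjusted threshold, and it sizes the trial as though there were one test.

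Three stronger readings should be resisted.
- A reader might multiply six subscales by 12 assessments to get 72 primary ANOVAs. The article describes the subscales but nowhere says that each is tested as primary, and one POMS figure per arm in {14} points to a single score. If several subscales were tested as primary, the error would be higher than in the table, but that is conditional.
- A reader might multiply again by three pairs to get 216 tests, or blame the absence of a named contrast. Step 4 shows that the pairs do not add to the error within a time point. Which contrast matters most is a question of interpretation.
- A reader might conclude that the trial is too small. On its own figures it is not.

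Two further points have some force. The 7:00 session is labelled baseline, so 10 sessions may be the fairer count; this trims the range to about 13–37%. Ratings taken every 3 h may also be highly correlated, which favours the lower end. Even there the rate is more than double 5%.

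**Conclusion.** The concern holds in this form: the primary score and time are undefined, and POMS is tested at every time point by separate unadjusted ANOVAs, against a sample size built for one POMS value at one alpha. For one score over 11 sessions the false-positive rate is about 14–31% with equal within-person correlation of 0.9 to 0.5, or 21–39% with AR(1) correlation over the same range, against a nominal 5%. These figures rest on two assumptions: the correlation, which the article does not give, and that significance at any time would count as primary success, which the article neither states nor excludes. The defect touches the trial's main claim and should be corrected.

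**What to change.** Amend the primary outcome section {12} and the statistical methods section {20a} to name as primary the POMS score that produced 8.26, 18.25 and 15.24. Then choose one of two routes:

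- **(a) One primary time.** For example the 30-h session (13:00 on day 2), which matches the title. Other times are defensible, given the time-point objective in {7}. All other POMS times and subscales, PANAS and FaceReader become secondary. The test may be one omnibus ANOVA followed by Student-Newman-Keuls, or AE vs NAE and then AE vs blank in fixed order.
- **(b) All sessions confirmatory.** Apply Bonferroni or Holm across times to the named score. This serves the time-point objective without demoting any session.

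Timing matters. The trial status section puts first enrolment at 20 November 2020 and the end of recruitment at 20 May 2021, before the article appeared on 1 November 2021. The choice is credible only if it is dated and documented before unblinding. Since {17b} runs the analysis after a first, coded unblinding, that step is the one it should precede.

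The cost is wording, plus loss of confirmatory status for the other times under (a) or some power under (b). Step 5 puts the power at 0.93 to 0.99 under (a) and about 0.89 to 0.91 under (b) with 11 per arm, so the planned 42 can stand.

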### Trial design {8}

This will be a single-center, single-blind, parallel-arm, randomized clinical trial. Forty-two healthy male volunteers will be allocated into the AE group, NAE group, or blank group with an allocation ratio of 1:1:1. This trial will comprise 1-week baseline (baseline sleep), 1-week preventative treatment, 30-h TSD, and 24-h after waking follow-up periods. Figure 1 shows the flow diagram of the trial.

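### ANOVA with Student-Newman-Keuls pools one variance although the pilot SDs differ up to 1.87-fold; if they hold, sham vs blank is tested at about 8.5% and the AE contrasts conservatively

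*Protocol article*

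**What the plan says.** In the protocol article, under Statistical methods for primary and secondary outcomes {20a}, the POMS, PANAS and FaceReader scores "will be compared among the three groups at all time points using ANOVA". The follow-up procedure is named: "The Student-Newman-Keuls method will be used for pairwise comparisons". The threshold comes under "Statistical significance will be set at" p ≤ 0.05. The normality condition in that section decides only whether the mean (SD) or the median is reported. It does not change the test.

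Under Sample size {14}, "the means of the POMS scores for each group are 8.26, 18.25, and 15.24", "with standard deviations of 3.18, 5.96, and 5.42, respectively". The arms are listed there as AE, NAE, blank, so the values are read in that order. The same section states that "at least 33 subjects will be needed in our study if the power is 0.9", and then "To compensate for a 20% loss to follow-up, the sample size will be increased to 42 participants". Allocation is "with an allocation ratio of 1:1:1", which gives 14 per arm.

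The Interventions section uses NAE to separate out placebo effects and the blank arm to judge whether EA works, and announces comparisons between all three groups.

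**The concern.** Student-Newman-Keuls (SNK) divides every pairwise difference by a standard error built from the variance of all three arms. This is right only if the arms share a variance, and the plan's own planning figures say that they do not: the largest SD is 5.96/3.18 = 1.87 times the smallest, a variance ratio of 3.5. Pooling lets the small AE variance shrink the standard error for the two control arms, and lets the large control variances widen it for the AE contrasts. Equal arm sizes largely protect the overall F test but not the pairwise tests, because the bias sits in each pairwise standard error.

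A three-arm trial is read on its pairwise comparisons. NAE vs blank shows whether needling at non-acupoints alone changes mood, and in the pilot these arms already differ by 18.25 − 15.24 = 3.01 points. A difference there would be declared too readily. AE vs blank and AE vs NAE would be tested more strictly than intended.

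**Working it through.** **Inputs.** Pilot means 8.26, 18.25, 15.24; pilot SDs 3.18, 5.96, 5.42; 33 participants (11 per arm) before dropout and 42 (14 per arm) after; α = 0.05, taken as two-sided because the sidedness is not stated. Normal data are assumed in the simulations.

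**The plan's sample size.** The PASS procedure is not named.
- Noncentral-F calculation for one-way ANOVA: 24 in total with the root-mean-square SD, 30 with the largest SD. Neither is 33.
- AE vs blank (15.24 − 8.26 = 6.98) tested by SNK with the pilot SDs: simulated power 0.872 at 10 per arm and 0.908 at 11 per arm, hence 33.
- A two-sample formula at α = 0.05/3 with SD 4.443 also gives 11 per arm.
- Dropout: 33/0.8 = 41.25, rounded up to 42 for three equal arms.

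So 33 and 42 reproduce, with 33 as a pairwise figure.

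**SD used against SD needed.**
- Pooled: √[(3.18² + 5.96² + 5.42²)/3] = √(75.01/3) = 5.00
- NAE vs blank: √[(5.96² + 5.42²)/2] = 5.70
- AE vs blank: √[(3.18² + 5.42²)/2] = 4.44
- AE vs NAE: √[(3.18² + 5.96²)/2] = 4.78

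The ratios of true to pooled standard error are 1.139, 0.889 and 0.955.

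**Approximate error of a two-mean comparison.** At 14 per arm there are 39 degrees of freedom and the critical t is 2.023. The actual error is 2·P(t₃₉ > 2.023/ratio):
- NAE vs blank: 2.023/1.139 = 1.776, giving 8.4%
- AE vs blank: 2.023/0.889 = 2.276, giving 2.8%
- AE vs NAE: 2.023/0.955 = 2.118, giving 4.1%

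**Simulation of the full procedures** (14 per arm, pilot SDs, 200,000 to 400,000 trials per scenario). The Welch column is Welch's ANOVA as a gate, then Welch t-tests.

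| Scenario | Contrast | SNK | Welch |
|---|---|---|---|
| NAE = blank, AE 6.98 lower | NAE vs blank | about 8.5% | 5.0% |
| AE = blank, NAE clearly different | AE vs blank | 3.0% | 5.0% |
| AE = NAE, blank clearly different | AE vs NAE | 4.2% | 5.0% |
| All three equal | NAE vs blank | about 4.5% | 2.5% |
| All three equal | AE vs blank | about 1.5% | 2.5% |
| All three equal | any rejection | about 5.5% | 5.0% |

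With equal SDs, SNK gives 5.0% in each of the first three rows and about 2.4% per pair when all three arms are equal. The first three SNK rates are practically the same at 11 per arm.

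**Rejection rates at the pilot means.**

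| Contrast | Per arm | SNK | Welch |
|---|---|---|---|
| AE vs blank | 11 | 0.908 | 0.931 |
| AE vs blank | 14 | 0.965 | 0.977 |
| NAE vs blank | 14 | 0.36 | 0.27 |

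AE vs NAE exceeds 0.99 under both procedures at 14 per arm.

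**Sensitivity to the SD ratio.** With both controls sharing one SD, 1.25 to 1.5 times that of AE, the t approximation gives 6.5-7.6% for NAE vs blank and 4.3-3.8% for AE vs blank.

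**The case against.** The best defence has four parts.

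- **The rates are conditional.** A reader might infer that one trial carries both the 8.5% and the 3%. It cannot: the first needs NAE equal to blank with AE clearly apart, the second AE equal to blank with NAE clearly apart. If no arm differs, the overall error is close to nominal. This stands. Only the first scenario is near the plan's expectation, since the pilot AE mean lies about 7 points below blank and 10 below NAE.
- **No false claim of benefit.** A reader might also infer that a positive AE result is less trustworthy. The figures do not support that: both AE contrasts run below 5%, and AE vs blank loses about one point of power at 14 per arm. The 3% figure also needs AE to match the mean of blank while keeping a much smaller SD. With AE at the blank SD of 5.42, the rate is 4.3%. This stands too.
- **The SDs are uncertain.** The pilot size, time point and POMS score definition are not given. Assuming 10 per pilot arm, a 95% interval for the ratio 5.96/3.18 runs from about 0.93 to 3.8; assuming 20, from about 1.2 to 3.0. Nor does one set of POMS SDs show the same pattern in PANAS or FaceReader. This limits the size of the effect, not its direction when AE is the less variable arm.
- **A SAP may add a variance check.** A missing check would be no finding. But the article names a pooled-variance method outright, and its own planning figures speak against that method. This part does not remove the point.

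**Conclusion.** The point holds in limited form. The article commits to a pooled-variance pairwise procedure although its own pilot SDs contradict equal variances. If those SDs hold, NAE vs blank has a type I error of about 8.5% instead of 5% when AE differs clearly. The AE contrasts err on the strict side, at about 3% for AE vs blank and 4.2% for AE vs NAE, each when the third arm differs clearly. The distortion therefore falls on the reading of sham against no treatment, not on the efficacy claim, and it does not call the 42 participants into question. The figures rest on normal data, 11 to 14 analysed per arm in equal numbers, and pilot SDs of unknown precision; a milder SD ratio shrinks the effect. Severity is minor to moderate.

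**What to change.** Under Statistical methods for primary and secondary outcomes {20a}, replace one-way ANOVA with SNK by Welch's ANOVA at 0.05 followed, only if significant, by Welch (unequal-variance) t-tests for the three pairs, each at 0.05. With three arms this is a closed procedure, so no further adjustment is needed within a comparison of the three groups. Report each pairwise difference with a 95% confidence interval on the same unequal-variance basis.

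The change is one line of text, uses standard software output and needs no more participants. The cost is slightly fewer degrees of freedom and a lower, but correctly calibrated, rejection rate for NAE vs blank (about 0.27 instead of 0.36 at the pilot means, 14 per arm). On the pilot figures the AE contrasts lose no power.
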